**1. Introduction**

- 1. **Background**

Fever without source (FWS) is defined as a fever 38.0°C/100.4°F and above for less than 7 days with no underlying cause despite a thorough history and physical exam^[[1]](#endnote-1),^^[[2]](#endnote-2)^. Most children below 3 years old presenting with FWS have a self-limited viral infection. However, 10 to 25% of children have an underlying serious bacterial infection (SBI), such as pyelonephritis or pneumonia, or an invasive bacterial infection (IBI), such as meningitis or bacteremia, which can present only as FWS in the early stages^[[3]](#endnote-3)^. Because of lack of specificity in symptoms and signs^[[4]](#endnote-4),^^[[5]](#endnote-5)^, diagnosis is frequently supported by biological exams. Besides blood tests, more invasive laboratory procedures such as lumbar puncture and urinary catheterization are often required. Empirical administration of broad-spectrum antibiotics to prevent SBI cases are often prescribed. Differentiating viral from bacterial infections in children with FWS could avoid invasive investigations and useless antibiotic prescription.

Routinely used microbiological diagnostic tests such as culture, serology, and more recently nucleic acid-based tests (e.g., RT-PCR) can assist the clinician in the etiological determination of the underlying infectious process. However, several challenges remain, including : (i) pathogen detection in cases where the infection site is not readily accessible (e.g., pneumonia), or is unknown (e.g., fever without source); (ii) time to microbiological laboratory results may be lengthy (hours or days); (iii) determination whether a detected bacteria is the disease causative agent or a mere colonizer^[[6]](#endnote-6),^^[[7]](#endnote-7),^^[[8]](#endnote-8)^, and (iv) identification of a virus does not preclude the possibility that an undetected bacteria may be the cause of the underlying illness (i.e. a case of mixed infection with both virus and bacteria)^[[9]](#endnote-9)^.

These challenges can be addressed through monitoring the host's immune response to infection, rather than direct pathogen detection. Proteins that are routinely used to support diagnosis of bacterial infection include procalcitonin (PCT) and C-reactive protein (CRP). However, these markers are sensitive to inter-patient variability, including time from symptom onset, clinical syndrome, and pathogen species^3,^^[[10]](#endnote-10)^. For example, multiple studies found that procalcitonin is valuable for guiding antimicrobial therapy duration and for predicting disease severity^[[11]](#endnote-11),^^[[12]](#endnote-12),^^[[13]](#endnote-13)^. However, its diagnostic accuracy for detecting bacterial etiology in sepsis and pneumonia has been challenged. Elevated CRP levels are suggestive of a bacterial infection^3,^^[[14]](#endnote-14)^, but similar levels may be observed in patients with some viral strains (e.g., adenovirus and influenza)^[[15]](#endnote-15)^, and inflammatory diseases.

Whereas most biomarkers or combinations of biomarkers are responsive to bacterial infections, a new assay (ImmunoXpert) intended for children aged 90 days and more and adults has been recently developed^12,^^[[16]](#endnote-16),^^[[17]](#endnote-17),^^[[18]](#endnote-18)^. This assay measures the concentration of three host-related, serum-based protein biomarkers and combines their levels into a single score that determines the likelihood of bacterial or viral immune response. The score is computed using a predetermined logistic regression formula that was developed and tested on previously collected cohort of >2000 patients. It combines for the first time two viral-induced biomarkers, tumor necrosis factor-related apoptosis-inducing ligand (TRAIL) and interferon γ-induced protein-10 (IP-10), with a bacterial-induced one, C-reactive protein (CRP)^6^. Using predetermined score cut-offs each one of the patients will be classified as having bacterial, viral or equivocal immune response (i.e., inconclusive). It displays three possible outcomes: (1) Viral infection (or non-bacterial aetiology): ImmunoXpert score < 35; (2) Equivocal: 35 ≤ ImmunoXpert score ≤ 65; and (3) Bacterial infection (including mixed bacterial and viral co-infection): ImmunoXpert score > 65.

**1.2 Previous work justifying this trial**

A recent study using the novel ImmunoXpert assay as a single ELISA test, proved to be outstanding in discriminating bacterial from viral infection, without the need to directly sample the infection site and with the ability to differentiate between pathogenic strains of bacteria or viruses and colonizers^[[19]](#endnote-19)^. This signature has already shown high diagnostic accuracy in a heterogeneous study population of febrile inpatients and emergency department arrivals, both children and adults, presenting with diverse clinical syndromes and pathogens^12,^^[[20]](#endnote-20),^^[[21]](#endnote-21),^^[[22]](#endnote-22)^. Rapid (within minutes) and easy to use formats suitable for the point-of-care are under development.

The potential applicability of the TRAIL/IP-10/CRP assay and its comparison with other common biomarkers and the Labscore^3,^^[[23]](#endnote-23),^^[[24]](#endnote-24)^, a biological score based on weighted scoring of procalcitonin (PCT), C-reactive protein (CRP) and urinary dipstick results, has never been studied prospectively in a population of children with FWS. Moreover, limited data were available in the fragile subpopulation of patients aged under 90 days in whom the need is serious for improved diagnostic tools to drive decision-making^[[25]](#endnote-25),^^[[26]](#endnote-26)^. The purpose of this study is to assess the diagnostic accuracy of various individual and combined bacterial- and viral-specific biomarkers, notably the ImmunoXpert and the Labscore, in children and infants under and over 90 days old presenting with FWS.

**2. Methods**

**2.1 Objectives and hypothesis**

To determine the correlation of a combination of biomarkers: CRP with two new viral biomarkers (TNF-related apoptosis-inducing ligand (TRAIL) and Interferon gamma-induced protein-10 (IP-10) for the discrimination between viral or bacterial infections (SBI and IBI).

**Primary objective**

To prospectively investigate the diagnostic accuracy of a host signature (TRAIL, IP-10 and CRP) to reliably predict bacterial infections and to compare its performance to routine individual biomarkers (CRP, PCT, WBC, ANC, TRAIL and IP-10) and to the Labscore. Differential expression of biomarkers and combinatorial scores will be assessed in children with FWS and in control patients for the ImmunoXpert and its components.

**Secondary objectives**

To compare the diagnostic accuracy of the ImmunoXpert, the Labscore, and individual biomarkers to reliably predict IBI.

**2.2 Study design**

Prospective diagnostic accuracy study in infants and children with FWS aged less than 3 years old (consecutive sample).

**2.3 Participants**

**2.3.1 Enrolment**

The study focuses on pediatric patients under 3 years of age presenting to the Pediatric Emergency Department (PED) of Children’s Hospital, Geneva University Hospitals (HUG), with a diagnosis of FWS after a thorough history and physical examination. The physician in charge will describe the purpose and the procedure of the study, possible risks/benefits, as well as rights and responsibilities of participants. If the patient or parents/guardians agree to participate, they will be asked to sign an informed consent form (IC) except if estimated without the competency to understand its content. No analysis will be performed before the signature of the IC.

**2.3.2 Inclusion Criteria**

- Clinical diagnosis of FWS (fever for less than 7 days with no underlying cause determined by history and/or physical exam)
- Age < 3 years old
- Informed consent (IC) given by parent or legal guardian.

**2.3.3 Exclusion Criteria**

- Unavailable blood specimen
- Comorbidities predisposing to infections such as cancer, primary or secondary immunodeficiency, and iatrogenic immunosuppression.

**2.4 Study specimen collection**

After informed consent was obtained, demographic data will be recorded (age, se, as well as delay between fever onset and presentation, and maximum temperature before presentation. Patients will be assessed according to local and international guidelines and recommendations with white blood cell count (WBC), absolute neutrophil count (ANC), band count, CRP, PCT, urinary dipstick and culture, and blood culture. Additional testing (CSF culture, chest X-ray, synovial fluid or stool culture etc.) will remain optional, depending on the clinical evaluation.

An additional 0.6 mL sample will be drawn, to determine CRP, TRAIL and IP-10 values and the ImmunoXpert score. No venous puncture for the additional blood sampling will be performed specifically for the study. Blood sample will be drawn from the venous catheter only in case of venous reflux. No other blood sample nor biological exam will be required for the purpose of the study. No human genetic testing will be performed.

The use of sera from a group of 50 healthy Canadian children from trauma and dental clinics will serve as control patients for TRAIL and IP-10 values, after their use have been approved by Toronto’s Hospital for Sick Children Ethics Committee.

**2.5 Gold standard**

**2.5.1 Expert panel adjudication**

Expert panel adjudication will serve as reference standard. This is a common approach to assigning a final diagnosis in fields where gold standard is lacking, specifically in patients with FWS^[[27]](#endnote-27),^^[[28]](#endnote-28)^. For determining the disease etiology (bacterial or viral), each patient will be assigned a diagnosis set by an independent panel of 3 three senior pediatricians with >10 years of experience, each of which will be blinded to the diagnosis of his/her peers and to the assay results. The experts (one senior pediatric infectious-disease specialist and two senior pediatric emergency physicians) will independently perform an initial etiologic classification (viral, bacterial or indeterminate etiology). Then, they will be asked to independently classify patients with indeterminate diagnosis into suspected viral or bacterial infection, as recommended in most studies using this kind of reference standard. The combined results of the experts will permit to create the reference standard as a “majority” diagnosis: cases will be included under the etiology label assigned by minimum 2 of the 3 experts.

Other definitions of reference standard will also be investigated to assess the robustness of the findings: microbiological diagnosis and unanimous reference standard.

**2.5.2 Microbiological diagnosis**

A microbiological diagnosis will be established using below-mentioned predefined criteria to classify patients as follows: (1) bacteriologically proven SBI or IBI or (2) no proof of bacterial infection.

**Definition of SBI**

Microbiological serious bacterial infection is defined by isolation of a bacterial pathogen from any urine, synovial fluid, bone, or stool specimen. Microbiological urinary tract infection (UTI) will be defined according to the AAP Subcommittee on Urinary Tract Infection and Steering Committee on Quality Improvement and Management, based on a urine specimen obtained through urinary tract catheterization or clean catch of mid-stream urine^[[29]](#endnote-29)^:

- Patients > 60 days old: abnormal urinalysis defined by the presence of positive leukocyte esterase, nitrite or pyuria (>5 white blood cells (WBCs) per high-power field) and culture growth of at least 50’000 colony-forming units (cfu) per mL of a uropathogen
- Patients ≤ 60 days old: growth of 50’000 cfu/mL or more of a uropathogen, or growth of 10’000 cfu/mL or more of a single uropathogen in association with an abnormal urinalysis.

**Definition of IBI**

Invasive bacterial infection (IBI) is defined as isolation of a compatible bacterial pathogen in blood or cerebrospinal fluid culture.

**2.5.3 Unanimous reference standard**

Analyses will also be performed under a “unanimous” reference standard, whereby cases will be included in the analysis only if the same etiology label was assigned by all 3 experts, after exclusion of indeterminate cases.

**2.6 Methods of measurement and data collection**

Biological exams will be performed in the Laboratory Department at Geneva University Hospitals. Demographic and clinical data will be collected on case report forms (CRFs), and then entered on a secure institutional database.

**2.7 Power and sample size calculation**

The sample size of this ancillary study is driven by the main study on viremia in patients with FWS, in which a sample of 50 viremic patients is planned[^20^](#_ENREF_20). To reach this target, assuming a 10-20% prevalence of viremia, the enrolment of 400 patients is anticipated, but the enrolment of patients will terminate when the number of patients with viremia will corresponded to the target. A power calculation for this ancillary study is conducted to determine the detectable difference in area under the ROC curve (of any biomarker compared with the ImmunoXpert) with a power of 80% under various sample sizes (0.08 detectable difference with a sample size of 100 to 0.10 with a sample size of 264 patients). The power to detect a difference in areas under ROC curve should be acceptable for the evaluation of biomarker accuracy.

Concerning power calculation, we assume (1) a two-sided risk alpha of 0.05, (2) a correlation between ImmunoXpert and the other marker of 0.5 both in patients with a bacterial infection and in those with a viral infection and (3) a viral infection rate 3 times higher than that of bacterial infection. Using the method of sample size calculation for comparison of paired binormal ROC curves proposed by Obuchowski et al^[[30]](#endnote-30)^, the needed sample size is 264 patients (66 with a bacterial infection and 198 with a viral infection).

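### The two detectable AUC differences in the power statement run the wrong way (0.08 with 100 patients, 0.10 with 264), and the AUCs behind them are not stated

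*Protocol*

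**What the plan says.** Protocol section 2.7 sets out to find the "detectable difference in area under the ROC curve (of any biomarker compared with the ImmunoXpert"), "with a power of 80% under various sample sizes". The result is given in a parenthesis: "0.08 detectable difference with a sample size of 100 to 0.10 with a sample size of 264 patients". From this the section concludes that power should be acceptable.

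The assumptions follow, once for the whole calculation: "a two-sided risk alpha of 0.05"; "a correlation between ImmunoXpert and the other marker of 0.5 both in patients with a bacterial infection" and likewise in viral patients; and "a viral infection rate 3 times higher than that of bacterial infection". The method is Obuchowski's for "comparison of paired binormal ROC curves", and the outcome is that "the needed sample size is 264 patients (66 with a bacterial infection and 198 with a viral infection").

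Neither the AUC of the ImmunoXpert nor that of a comparator appears, and 264 is not expressly tied to a target difference. The same section says that enrolment is driven by the main viremia study: about 400 patients are anticipated, and recruitment stops once 50 viremic patients are reached. Section 2.10 names DeLong's method for comparing the AUCs.

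**The concern.** With everything but sample size held fixed, more patients must allow a smaller difference to be detected. The parenthesis says the opposite: 100 patients detect 0.08, while 264 detect only 0.10.

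This is the protocol's only power statement for comparing the ImmunoXpert with the other biomarkers and the Labscore, which is part of the primary objective. The final number is also not fixed in advance. At the assumed viremia prevalence of 10% to 20%, 50 viremic patients correspond to 50/0.20 = 250 up to 50/0.10 = 500 enrolled. A reader therefore needs a correct relation between sample size and detectable difference. As printed, the reader would credit 100 patients with 80% power for a difference of 0.08, and could read too much into a comparison that is not significant.

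**Working it through.** **Inputs from section 2.7.** Two-sided alpha 0.05 (z = 1.960); power 80% (z = 0.842); correlation 0.5 in both groups; ratio R = 3. So 264 patients are 66 + 198 and 100 patients are 25 + 75. **Assumed, because not stated:** ImmunoXpert AUC (A1) from 0.80 to 0.95, with comparator AUC A2 = A1 − d.

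**Formula.** The number of bacterial patients is n = (1.960·√V0 + 0.842·√VA)² / d², with VA = V(A1) + V(A2) − 2C(A1, A2), and N = 4n. C is the covariance from the paired correlation. In Obuchowski's approximation V(A) = 0.0099·exp(−a²/2)·[(5a² + 8) + (a² + 8)/R], with a = 1.414·Φ⁻¹(A). The full binormal variance was used as an alternative.

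**Can 264 be reproduced?** Yes, but not uniquely. With the full binormal variance, N = 264 results for d = 0.10 at A1 of 0.776–0.782, and for d = 0.08 at 0.886–0.888. With Obuchowski's approximation and V0 = VA, N = 264 for d = 0.10 falls at A1 of 0.947–0.948. The figure is attainable, but without its AUCs and target difference it cannot be verified.

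**Can the printed pair be reproduced?** No. For a given variance, d is proportional to 1/√N, and √(264/100) = 1.62:

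- 0.10 at N = 264 implies 0.10 × 1.62 ≈ 0.16 at N = 100.
- 0.08 at N = 100 implies 0.08 / 1.62 ≈ 0.05 at N = 264.

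Solving the formula at fixed ImmunoXpert AUC gives these detectable differences at N = 100 / 264 / 400:

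| ImmunoXpert AUC | Full binormal variance (null variance at A2) | Obuchowski approximation (V0 = VA) |
|---|---|---|
| 0.80 | 0.174 / 0.102 / 0.081 | 0.196 / 0.122 / 0.099 |
| 0.85 | 0.166 / 0.094 / 0.074 | 0.194 / 0.120 / 0.097 |
| 0.90 | 0.153 / 0.083 / 0.065 | 0.189 / 0.114 / 0.091 |
| 0.95 | 0.134 / 0.066 / 0.049 | 0.175 / 0.099 / 0.077 |

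Over all binormal variants tried, the ranges are 0.078–0.196 at 100, 0.046–0.122 at 264 and 0.036–0.099 at 400. The lowest value at 100 comes close to 0.08, but that does not rescue the pair. At each fixed ImmunoXpert AUC the difference at 100 is about 1.6 to 2.0 times that at 264, so 0.078 at 100 goes with at most about 0.078/1.6 = 0.049 at 264.

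**Power of the planned test.** Paired binormal data, DeLong test, 1500 runs per cell; where two independent sets of runs differ, both results are shown:

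| ImmunoXpert AUC | d = 0.08, N = 100 | d = 0.10, N = 264 | d = 0.08, N = 400 |
|---|---|---|---|
| 0.80 | 28–29% | 79–80% | 80% |
| 0.85 | 35% | 87% | 89% |
| 0.90 | 41–44% | 95% | 95% |
| 0.95 | 56–59% | 99% | 100% |

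Runs differ by a few points. Taken together, power for 0.08 with 100 patients is about 29% to 60%.

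**Would a swap repair it?** No. Going from d = 0.10 to d = 0.08 multiplies N by about (0.10/0.08)² = 1.56, whereas 264/100 = 2.64. With the full binormal variance, 0.10 at N = 100 needs A1 of 0.975–0.980, while 0.08 at N = 264 needs 0.886–0.888.

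**The case against.** The strongest defence is that the two ends need not share an AUC. In simulation, 0.08 with 100 patients has 78% power at an ImmunoXpert AUC of 0.98 and 86% at 0.99, and 0.10 with 264 has about 80% at 0.80. So the figures could coexist under different AUCs. That stands as arithmetic, and it is why the contradiction must be stated as one at a common AUC. But section 2.7 neither gives an AUC nor says that it varies; only sample size does.

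The second defence concerns consequence. The main study drives enrolment, so correcting the sentence changes no recruitment number, test or estimate. This stands too.

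Several stronger readings are tempting, and the protocol does not support them:

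- **That the study is underpowered.** At 264 patients, simulated power for 0.10 is about 78% to 99% over the assumed AUCs, and 400 patients are anticipated. The judgement that power is acceptable may well be right; the printed pair does not show it.
- **That 264 reveals an assumed AUC near 0.95.** This depends on the variance formula. Under the DeLong test, power for 0.95 against 0.85 with 264 patients is already 99%, so 0.10 is not the smallest detectable difference there.
- **That 100 was meant as the bacterial count of 400.** The arithmetic is suggestive: 400/4 = 100, and 0.10·√(264/400) = 0.081. The text does not say so, and only the sponsor can confirm it.
- **That the protocol plans to treat non-significance as equivalence.** It makes no such claim. The risk lies in how a reader would use the power figure.

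**Conclusion.** The power statement is wrong as written. With alpha, power, correlation and case mix fixed, 0.08 at 100 patients and 0.10 at 264 cannot both hold at any common AUC, and nothing elsewhere in the protocol corrects it. The direction of the error needs no assumed AUC.

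Its size does need one. If the 264-patient end is right, the difference detectable with 100 patients is about 0.16 by simple scaling, twice the printed value. If the ImmunoXpert AUC lies between 0.80 and 0.95, with binormal markers, the power of the DeLong test for 0.08 with 100 patients is about 29% to 60%. The missing AUCs are part of the same fault, because without them neither the pair nor 264 can be checked. The error is confined to the stated power and the reading of non-significant comparisons.

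**What to change.** In section 2.7:

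- State the AUC assumed for the ImmunoXpert and for the comparator, and the target difference that 264 patients are meant to detect.
- From that one set of assumptions, recompute the difference detectable at 80% power with 100, 264 and 400 patients, giving the bacterial and viral counts for each. Use a method consistent with the DeLong test in section 2.10, for example by checking the formula against a simulation of that test.
- Replace the parenthesis with these figures. Do not simply exchange the two differences. Say whether 100 was meant as a total or as a number of bacterial cases.
- Since the AUCs are uncertain, show the result for more than one plausible value.

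The cost is a short calculation and one restated sentence. No patients, procedures or analyses are added.

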**2.8 Blinding**

Experts will access to full medical records but will remain blinded to the diagnosis of their peers and to TRAIL, IP-10 and ImmunoXpert results; CRP, PCT and urinary dipstick data will be available to the experts to determine the etiology label. The ImmunoXpert test will be performed on anonymized samples. The index test and panel expert reference standard outcomes will be locked prior to unblinding.

**2.9 Confidentiality**

Relevant patient data will be recorded on individual case report forms (CRFs) under an individual identifying code assigned to each participant that does not provide any identifying information. Data will be entered on the day of enrolment and after definitive laboratory results by study investigators. The information contained within the CRFs will be transferred to a computerized database and will be exclusively accessible to the study team. Data will be encoded with the date of birth and stored for 10 years.

**2.10 Statistical analysis plan**

Biomarkers will be described in patients with bacterial and viral infections by median and interquartile intervals. Mann-Whitney test will be used to compare these groups. Diagnostic performances of biological scores and markers in identifying bacterial infections will be assessed by non-parametric ROC curves. The areas under the ROC curves will be assessed and compared using the non-parametric approach proposed by Delong et al^[[31]](#endnote-31)^. This approach accounts for paired data when two compared markers are measured in the same person. Sensitivities and specificities will be reported with the Clopper-Pearson exact 95% confidence intervals. The two-sided risk alpha will be 0.05 in all comparisons. Software used for statistical analyses will be R version 3.5.2 (R Core Team (2018). R: A language and environment for statistical computing. R Foundation for Statistical Computing, Vienna, Austria. URL <https://www.R-project.org/>).

No interim analyses will be performed as the implication for the patient is short in duration and doesn’t show any serious potential outcome.

